### Qualitative evaluation

In cohort 2, we will also evaluate satisfaction with the decision-making process and proactive care planning (including end-of-life discussions) through interviews after patients receive counselling with OncologIQ Palliative. Several days after the consultation, patients will be asked to participate in an interview. If they agree, they will be interviewed 3–4 weeks after receiving the prognostic information, and additional IC will be collected. The researcher will interview the patients using a structured interview guide, and the interview will be recorded. The interview will then be transcribed word for word. We will conduct these interviews either in person at the outpatient clinic, at the patients’ home, or by telephone, based on the patients’ preferences. The inclusion of patients will start simultaneously with the start of cohort 2.

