### Qualitative evaluation

In cohort 2 we will use a purposive sampling method to select patients, striving for a reflection of the patient group in terms of sex, age and tumour location. There are no additional selection criteria for participating in the interview. We cannot calculate a specific sample size due to the qualitative design. Therefore, we will continue including patients upon data saturation is achieved.

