To measure decisional conflict, patients will be asked to complete the Decisional Conflict Scale (DCS) questionnaire two weeks after the consult in which they received counselling. This can be done either online or by telephone. Therefore, the DCS is integrated into Healthcare Monitor, our electronic system for measuring patient-reported outcome measures (PROMs), enabling us to digitally send it to patients [37]. Data on QoL will be obtained using the EORTC QLQ-C15-PAL questionnaire, which is already included in Healthcare Monitor and is also part of our standard care for all patients with HNSCC in the palliative phase. The patient and tumour characteristics, such as smoking behaviour, ACE-27, and WHO-performance status will be collected at baseline. Additionally, data on palliative treatment, palliative sedation or euthanasia and overall survival will be gathered from the electronic patient files (EPFs).

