### Timeline

All patients will be actively participating for 1–2 months. During this period, they will complete the EORTC QLQ-C15-PAL questionnaire every 6–8 weeks, the DCS questionnaire 2 weeks after counselling, and possibly participate in an interview 3–4 weeks after counselling. Following this period, patients will no longer be actively involved in the study, as we will gather additional data from the EPF. This data will be collected from every patient over the course of the study (See Figs. 1 and 2 for an overview of the different steps and timeline).

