### Qualitative evaluation

The primary outcome relates to the effect of prognostic counselling on satisfaction with the decision-making process and proactive care planning. This includes end-of-life discussions on preferred place of death and wishes for palliative sedation and euthanasia. It will be assessed through interviews conducted with patients in cohort 2 after they receive counselling using the model.

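### Minor: sampled cohort 2 patients are invited to the interview before the two-week DCS, a contact cohort 1 does not have; invite after the DCS instead

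*Protocol article*

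**What the plan says.** The interview procedure is in the protocol article, under Recruitment and study procedures, Qualitative evaluation. It applies to one cohort: "In cohort 2, we will also evaluate satisfaction with the decision-making process and proactive care planning". The approach is timed as follows: "Several days after the consultation, patients will be asked to participate in an interview". For those who agree, "they will be interviewed 3–4 weeks after receiving the prognostic information, and additional IC will be collected".

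The part on the clinical study under the same heading has patients "complete the Decisional Conflict Scale (DCS) questionnaire two weeks after the consult in which they received counselling", online or by telephone. The Timeline section repeats the order of the two measurements: "the DCS questionnaire 2 weeks after counselling, and possibly participate in an interview 3–4 weeks after counselling".

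The section on sample size limits who is approached: "In cohort 2 we will use a purposive sampling method to select patients", with inclusion continuing until saturation, so no number is fixed. For cohort 1 the article describes study information and consent at the nurse practitioner visit, and no further research contact before the DCS.

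**The concern.** The DCS is filled in by patients who know how they were counselled. By the article's own description (Outcome evaluation), it covers feeling informed, feeling supported and being satisfied with the choice. The interview is about satisfaction with the decision-making process and with care planning, including "end-of-life discussions on preferred place of death and wishes for palliative sedation and euthanasia". The two subjects overlap closely. A request to talk about that subject, made in one cohort shortly before the questionnaire, is a difference between cohorts that has nothing to do with the prognostic model. If it moved answers at all, the movement would be counted as part of the model's effect.

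A second gap has the same source. No sentence says that the DCS must be in hand before the interview takes place, so a questionnaire returned late could follow a full recorded conversation about the decision.

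**Working it through.** **Order of events, counted from counselling**

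| Step | Time stated | Cohort 1 | Cohort 2 |
|---|---|---|---|
| Study information and consent | nurse practitioner visit after the consultation | yes | yes |
| Interview invitation | several days (no exact day) | none described | purposive sample |
| DCS | 2 weeks (day 14) | yes | yes |
| Interview | 3–4 weeks (days 21–28) | none | those who agree |

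If several days is read as fewer than 14, the order is invitation, DCS, interview. The interview comes after the DCS falls due, and only the invitation comes before it. For an interview to precede the DCS, the questionnaire would have to be at least 21 − 14 = 7 days overdue for the earliest interview, or 28 − 14 = 14 days for the latest.

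**The plan's own figure.** From the sample size section: difference 8, SD 17, α 0.05 (taken as two-sided), power 0.80.

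n = 2 × (1.960 + 0.842)² × 17² / 8² = 70.9, so 71 per group (72 with the t-test).

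The stated 79 is not reproduced. An unstated 10% allowance for dropout would give it (71 / 0.9 = 78.9). The difference is on the safe side and has no bearing on this point. With the planned 80 per cohort, power is 0.845 (normal approximation).

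**How large could an effect be?** The article gives no input for this, so the following is illustration only. Let f be the fraction of cohort 2 invited before the DCS and b the change in DCS per invited patient. Both are assumed.

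- Shift in the cohort mean: s = f × b.
- Standard error of the difference: SE = 17 × √(2/80) = 2.69.
- Two-sided type I error with no true effect: 1 − Φ(1.96 − s/SE) + Φ(−1.96 − s/SE).

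| f (patients of 80) | b (points) | s (points) | s as share of 8 | Type I error |
|---|---|---|---|---|
| 0.15 (12) | 2 | 0.3 | 4% | 0.051 |
| 0.25 (20) | 1 | 0.25 | 3% | 0.051 |
| 0.25 (20) | 2 | 0.5 | 6% | 0.054 |
| 0.25 (20) | 4 | 1.0 | 12.5% | 0.066 |
| 1.00 (80) | 2 | 2.0 | 25% | 0.115 |

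The sign of b is unknown. With a true difference of 8, a 0.5-point shift takes power from 0.845 to 0.885 if it favours the model and to 0.797 if it works against it. The last row of the table would need the whole cohort to be invited, which the purposive sampling does not suggest.

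**The case against.** The strongest defence is that the order that matters most is already right: the DCS is due at two weeks and the interview comes one to two weeks later. What precedes the DCS is a request to take part. The article does not say who makes it, by what route or in what words, and it does not say when the additional consent is taken, which may be at the interview itself. Return windows and reminders for the DCS are details that a full protocol would normally carry, and the timeline figure is not available here. All of this stands, and it keeps the point small. It does not remove it, because the early invitation is stated text and no sentence protects the DCS.

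A reader might also infer more than the article supports:

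- *That the whole intervention cohort is affected.* The sampling is purposive and the Timeline calls the interview only a possibility.
- *That the bias favours the model.* Being asked to reflect on a decision could raise or lower conflict. The article gives neither direction nor size.
- *That the interview is a co-intervention on palliative treatment and quality of life, on the strength of the Background.* The evidence cited there concerns end-of-life discussion with a physician. A research interview about satisfaction is a different thing, so the step does not follow.
- *That follow-up for the secondary outcomes should be cut at the interview date.* Doing so for interviewed patients in one cohort would make follow-up unequal and would itself bias the comparison. Interviewed patients have also survived and stayed well enough to take part at 3–4 weeks.

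**Conclusion.** The point holds as a minor, inexpensive improvement. As written, a purposive subset of cohort 2 is invited to an interview on satisfaction with decision-making before the two-week DCS, cohort 1 has no matching contact, and DCS completion is not a condition for either the invitation or the interview. This rests on reading several days as less than two weeks, which is the natural reading but is not stated as a rule.

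The effect on the primary comparison is probably small because only some patients are approached. With a quarter of the cohort invited and an assumed shift of 1–2 points each, type I error is 0.051–0.054. These figures show scale and are not estimates. The point does not call the trial's conclusions into question and does not extend to the secondary outcomes. It is worth acting on because the difference between cohorts is avoidable and easily prevented.

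**What to change.** In the Qualitative evaluation part of Recruitment and study procedures, replace the timing of the approach with a rule such as: *Patients in cohort 2 are asked to take part in an interview only after their DCS has been returned, or after its return window has closed; no interview takes place before then.* Keep the interview at 3–4 weeks, and record the invitation and interview dates.

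The clause on the closed window keeps DCS non-responders eligible, so that the qualitative sample is not limited to those who returned the form. The window should be the same in both cohorts and should close before the interview. A form still outstanding then counts as missing, so no DCS used in the analysis can follow an interview.

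Sample size, α and power do not change. The cost is time for scheduling. If invitations now go out at about day 7 (assumed), there are 14–21 days until the interview; from day 14 there are 7–14, and fewer where the team waits for the window to close. A few candidates may be lost as a result.

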### Timeline

All patients will be actively participating for 1–2 months. During this period, they will complete the EORTC QLQ-C15-PAL questionnaire every 6–8 weeks, the DCS questionnaire 2 weeks after counselling, and possibly participate in an interview 3–4 weeks after counselling. Following this period, patients will no longer be actively involved in the study, as we will gather additional data from the EPF. This data will be collected from every patient over the course of the study (See Figs. 1 and 2 for an overview of the different steps and timeline).

**Fig. 1 Fig1:**
[figure not shown]
Flowchart illustrating the different study procedures

**Fig. 2 Fig2:**
[figure not shown]
Flowchart illustrating the timeline of study procedures for patients involved in the clinical study and qualitative evaluation

### Outcome evaluation

#### Clinical study

The first outcome measure relates to the amount of decisional conflict and satisfaction with the decision-making process of patients after prognostic counselling. This will be assessed through a comparison of cohort 1 and cohort 2 on decisional conflict scores, measured using the DCS questionnaire (Appendix A) [38, 39]. This questionnaire measures: (a) personal perceptions of uncertainty in choosing options, (b) modifiable factors contributing to uncertainty, such as feeling uninformed, unclear about personal values, and unsupported in decision making, (c) effective decision making, such as feeling the choice is informed, values-based, likely to be implemented, and expressing satisfaction with the choice.

The secondary outcome measures relate to the effect of prognostic counselling on different factors, including: (1) overall survival, (2) palliative treatment, and (3) QoL.

*Overall survival* will be measured from the date of the start of the palliative trajectory until the date of death or the last follow-up visit. Survival outcomes will be compared between both cohorts.

*Palliative treatment* will be assessed by examining whether a patient underwent treatment and the type of treatment received. Data on treatment modalities will be collected for each patient by consulting the EPF.

*Quality of life (QoL)* of patients will be measured using the EORTC QLQ-C15-PAL questionnaire, a shortened version of the EORTC QLQ-C30 [40, 41]. This questionnaire is recommended for use in patients with advanced and incurable cancer with a short life expectancy. The EORTC QLQ-C15-PAL questionnaire consists of 15 questions across 10 domains: physical functioning, emotional functioning, fatigue, pain, dyspnoea, insomnia, appetite loss, constipation, nausea/vomiting, and global health status. In the domains of emotional functioning, physical functioning, and global health status, a higher score indicates a better QoL, while in the other domains, a lower score indicates a better QoL.

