### Recruitment and study procedures

#### Clinical study

Patients who are transitioning into a palliative HNSCC trajectory will be consecutively approached to participate in the study. The investigator will start by screening eligible patients after their first or follow-up visit. Once the patient has been discussed in the RWHHT, the researcher will check whether the palliative trajectory is confirmed.

In cohort 1, during the visit in which the palliative trajectory is discussed, the physician will provide counselling without the individualized prognostic model. As part of standard care, the patient will then visit the nurse practitioner immediately after their appointment with the physician. During this visit, the nurse practitioner or the investigator will inform patients about the study and present the subject information sheet. Patients will be asked to participate, and the informed consent (IC) form will be collected digitally.

In cohort 2, during the visit in which the palliative trajectory is discussed, the physician will inform the patient about the option to receive additional individualized prognostic counselling on their life-expectancy using OncologIQ Palliative. Considering that most patients have prognostic inquiries when discussing the palliative trajectory (*‘Doctor*,* how long will I live?’)*, we would like to offer them the model’s prognostic information directly or in a follow-up consultation, according to their preference. We believe it is unethical to let them wait for several days if they want to receive more prognostic information right away. If patients opt not to receive their individually calculated prognosis, they will be counselled without the model and offered general information about prognosis. However, if patients prefer not to receive any information on prognosis, their preference will be respected. As part of standard care, the patient will directly visit the nurse practitioner after their appointment with the physician. During this visit, the nurse practitioner or the investigator will provide the patient with additional oral information and the subject information sheet. We will only inform patients if they have received counselling with the model. If these patients wish to continue participating, we will ask them to sign the IC digitally.

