The overall survival function in both cohorts will be analysed using the Kaplan-Meier method. Statistical significance will be assessed using the log-rank test. Other secondary outcomes will be analysed using various tests, depending on whether the variable is continuous or categorical and whether it is normally distributed. A p-value of < 0.05 will be considered statistically significant for all analysis.

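### Cohort 2 patients who defer model counselling enter the study after the survival clock has started, and their DCS falls later after the palliative visit than in cohort 1

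*Protocol article*

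**What the plan says.** All references are to the protocol article.

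- **Counselling and entry, cohort 1** (Recruitment and study procedures, Clinical study): "In cohort 1, during the visit in which the palliative trajectory is discussed, the physician will provide counselling without the individualized prognostic model". The nurse practitioner visit follows immediately, and the study is explained and consent requested there.
- **Counselling and entry, cohort 2** (same section): patients are offered the model's "prognostic information directly or in a follow-up consultation, according to their preference". On study entry: "We will only inform patients if they have received counselling with the model". Consent is then sought from that group: "If these patients wish to continue participating, we will ask them to sign the IC digitally".
- **Survival** (Outcome evaluation, Clinical study): this endpoint "will be measured from the date of the start of the palliative trajectory until the date of death or the last follow-up visit", with one wording for everyone. On its use, the section adds: "Survival outcomes will be compared between both cohorts". The Statistical analysis section plans Kaplan-Meier curves and says: "Statistical significance will be assessed using the log-rank test". Cox regression is planned for influencing factors. The article mentions neither delayed entry nor a landmark.
- **DCS** (Recruitment and study procedures, Clinical study): completed "two weeks after the consult in which they received counselling". The Timeline section repeats the two weeks.

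**The concern.** The survival clock and the entry condition start together in cohort 1 but can come apart in cohort 2. A cohort 2 patient who chooses a later consultation and dies or becomes too ill before it is never told about the study and never appears in the data. A cohort 1 patient with the same course can be in the data from the day of the visit. Counting survival from the palliative start without adjusting for late entry therefore credits the deferring cohort 2 patients with days on which they could not have been observed to die.

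This matters because the authors expect fewer palliative treatments in cohort 2. The survival comparison will naturally be read as showing whether that comes at a cost, and a built-in advantage for cohort 2 could hide a small one.

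The same option moves the primary outcome. Two weeks after counselling is two weeks after the palliative visit in cohort 1, but two weeks plus the deferral in a deferring cohort 2 patient. Part of any DCS difference could then reflect time since the palliative discussion rather than the model.

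**Working it through.** The article gives no figure on this point to reproduce. The check asks how large the artefact would be with no true effect.

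**Inputs from the article.** Median survival is five months (Background and rationale), taken as 152.2 days. There are 80 patients per cohort (Sample size and power calculations). The DCS is at 14 days after counselling.

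**Assumptions.** Survival is exponential with no censoring. A share *f* of cohort 2 candidates defers by *d* days and enters only if alive at day *d*. The article gives neither *f* nor *d*; its only hint at length is a remark about a wait of several days.

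**Formulas.**
- Daily hazard: λ = ln 2 / 152.2 = 0.004554.
- Share of would-be deferrers dying before entry: q = 1 − exp(−λd).
- Share of deferrers among enrolled cohort 2 patients: p = f(1 − q) / (1 − fq).
- Apparent cohort 2 median: 152.2 − ln(1 − fq)/λ.
- Apparent rate ratio, cohort 2 to cohort 1: 1 / (1 + λpd), because mean survival in cohort 2 is 1/λ + pd.
- Mean day of the DCS after the palliative visit in cohort 2: 14 + pd (cohort 1: day 14).

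**Worked case, f = 50%, d = 14.** q = 1 − exp(−0.0638) = 0.062. p = 0.5 × 0.938 / (1 − 0.031) = 0.484. Rate ratio = 1 / (1 + 0.004554 × 0.484 × 14) = 0.970. Median = 159.1 days. Mean DCS day = 14 + 0.484 × 14 = 20.8.

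The table sets these formulas beside a simulation under the same assumptions: Cox hazard ratio from 200,000 patients per cohort, log-rank rejection from 3,000 trials of 80 per cohort.

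| d (days) | f | q | Median, cohort 2 (days) | Rate ratio, formula | Cox HR, simulated | Log-rank rejection | Mean DCS day, cohort 2 |
|---|---|---|---|---|---|---|---|
| 0 | – | 0 | 152.2 | 1.00 | 1.00 | 5.3–6.2% | 14.0 |
| 7 | 50% | 3.1% | 155.7 | 0.985 | 0.988 | 5.4% | 17.4 |
| 7 | 100% | 3.1% | 159.2 | 0.969 | 0.971 | 6.0% | 21.0 |
| 14 | 50% | 6.2% | 159.1 | 0.970 | 0.970 | 5.9% | 20.8 |
| 14 | 100% | 6.2% | 166.2 | 0.940 | 0.942 | 6.9% | 28.0 |
| 28 | 50% | 12.0% | 165.8 | 0.944 | 0.950 | 6.8% | 27.1 |
| 28 | 100% | 12.0% | 180.2 | 0.887 | 0.888 | 13.0% | 42.0 |

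The d = 0 row is the situation when entry and clock coincide: no spurious difference. Under the exponential assumption, delayed entry or a start at consent restores it, because the hazard after entry is the same in both cohorts.

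**Scale against sampling error.** With 80 deaths per cohort the standard error of the log hazard ratio is about √(1/80 + 1/80) = 0.158. A ratio of 0.97 is |ln 0.97| / 0.158 = 0.19 standard errors; 0.94 is 0.39.

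For the DCS, the arithmetic gives a shift in days only. The article contains nothing that converts days since the palliative visit into DCS points.

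**The case against.** The strongest reply is that the effect is small. For deferrals of up to a week the rate ratio stays at about 0.97 or above, well inside sampling error, and the false-positive rate of the log-rank test hardly moves. It reaches 13% only if every patient defers four weeks. The article points away from that extreme: it offers the information at the first visit, expects most patients to ask then, and regards several days as too long a wait for those who want it at once. The exponential model may also put too many deaths in the first days, since the article gives individual survival as ranging upward from one week. Survival is a secondary outcome. All of this stands as to size. It does not remove the mechanism, which is one-directional for deaths before entry and which nothing in the article corrects. Non-enrolment through deterioration would add to the selection and is not in the calculation.

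It is also fair that the start of the palliative trajectory is not defined. If it is the tumour board date, both cohorts share a short gap before the visit, and digital consent could lag in either. A reader might infer that guaranteed survival time exists in cohort 2 alone; only the extra gap among deferring patients is specific to that cohort.

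Two further inferences are tempting and not supported:

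- **That the later DCS favours cohort 2.** This assumes that scores fall between about two and four weeks after the palliative visit, which the article does not say. A deferring patient may also decide only after the second consultation, leaving the interval from decision to DCS much the same.
- **That ending follow-up at the last visit overestimates survival.** This requires deaths to be missed. The article collects survival from the patient files and does not say that deaths go unrecorded. If they are all captured, cutting survivors' time at an earlier visit would bias survival downward.

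**Conclusion.** The point holds. As written, the survival comparison counts time before enrolment for cohort 2 patients who defer, and the planned log-rank test does not allow for it. Under no effect and exponential survival with a five-month median, the spurious rate ratio is about 0.97 to 0.99 if up to all patients defer one week or half defer two weeks, and 0.94 if all defer two weeks. These values rest on assumed shares and lengths of deferral. Cohort 2 patients counselled with the model at the first visit are unaffected.

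The DCS timing difference is certain for deferring patients and concerns the primary outcome, but it establishes a confounded comparison, not a bias of known sign or size. The survival distortion is probably small. The reason to act is that it runs in favour of the intervention and costs almost nothing to remove.

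**What to change.** 1. **Survival.** Keep the palliative start as time origin and let each patient enter the risk set at the consent date (delayed entry) in the Kaplan-Meier, log-rank and Cox analyses, in both cohorts. Alternatively, start survival at consent in both cohorts. Delayed entry is the cleaner option because it keeps time since the palliative start comparable. State which date marks that start. Neither option corrects for patients who become too ill to return.
2. **DCS.** Keep it at two weeks after counselling. Moving it to a fixed time after the palliative visit is not advisable: at two weeks after that visit, a patient deferring two weeks would complete it on the day of model counselling, and one deferring longer would complete it before.
3. **Recording and sensitivity analysis.** Record the days from the palliative visit to counselling and to the DCS. Repeat the primary analysis with cohort 2 restricted to patients counselled with the model at the same visit. Because these patients chose immediate information, this is a sensitivity analysis and not a replacement.

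The cost is one extra date field, a slightly shorter counted survival and one more sensitivity analysis. Patients do nothing more.
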